### Study progression criteria

The findings from this feasibility study will be assessed against key progression criteria from the mixed methods process evaluation data to inform whether to proceed to a future larger trial. In terms of recruitment, as part of the screening process, we will identify the expected number of family carer dyads potentially eligible from each participating organisation’s database and the conversion rate of those who consented to participate [51], i.e. if we can recruit more than 10 dyads from 100 eligible dyads.

Regarding attrition rate, we will aim for a dyad drop-out rate of less than 20%, along with an assessment of the reasons for such loss.

Success for intervention adherence will be determined if there is more than 80% staff adherence to the intervention schedule (assessed via action logs). The intervention and trial procedures will be considered acceptable if there is data completeness of over 80% for each outcome measure and data collection method. The feasibility study could help with defining what adherence and engagement mean in the context of the future nutrition intervention trial. Determining progression criteria is seen as an essential element in assessing the success of a feasibility study [51].

Table 5 outlines the study progression criteria. We will use a traffic light system as a method to define targets for progression: green = progress, amber = amend, red = stop, in combination with data from the process evaluation. This system and findings will be monitored and reviewed by the Project Management Group and reported to the Project Steering Group for input interpretation and input [52].

**Table 5 Tab5:** TOMATO progression criteria

Domain	Proceed with RCT (Green)	Consider possible improvements (Amber)	Do not proceed (Red) (Red)
Recruitment	≥ 10% of eligible participants enrolled	5–9% of eligible participants enrolled	< 5% of eligible participants enrolled
Retention	≥ 80% of participants retained at follow up	50–79% of participants retained at follow-up	< 50% of participants retained at follow-up
Adherence	≥ 80% staff adherence to the intervention schedule (adherence is defined as setting at least four actions (as documented in the monthly action logs) to do things differently in response to using the resources).	50–79% of staff who adhere to the intervention schedule	< 50% of staff who adhere to the intervention schedule

### Data analysis

#### Quantitative

We will conduct quantitative data analysis primarily using descriptive statistics, including frequencies, means, and percentages with 95% confidence intervals (CIs) (using SPSS v26.0). Categorical data will be presented as frequencies and percentages.

Specifically, we will describe participants’ demographic characteristics and outcome scores collected at baseline and at 4 months using suitable summary statistics. We will also report the proportion of missing data for each outcome measure. We will calculate the differences between baseline and 4-month follow-up, with 95% CIs, for all outcome scores listed in Table 4. We will assess and estimate key progression indicators (using the traffic light system as in Table 5) and obtain stakeholder input to support interpretation of findings and decisions regarding proceeding to a larger trial [52]. These indicators will include recruitment rates, the proportion of homecare staff adhering to the intervention schedule (defined as setting at least four actions over the 4-month intervention period, documented in the monthly action logs), and the proportion of participating clients for whom the outcome measure questionnaire booklet was completed.

We will analyse resource use data collected during the final 1-month follow-up period. Cost will be estimated based on the most recent PSSRU Unit Costs of Health and Social Care [53], and the NHS Drug Tariff for medication costs [54]. Where the specific type of medication is uncertain, we will apply an average cost across all plausible options.

A CONSORT flow diagram will present the flow of participants through the study [37]. The number of participants approached, eligible, consented and enrolled and retained at follow-up will be reported along with reasons for withdrawal or dropout where possible. We will summarise and report rates and patterns of missing questionnaire data to inform the selection of outcomes and administration strategy for a full trial. A statistical analysis plan will be developed and reviewed by the Chief Investigator and Project Management Group prior to commencing analysis.

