### Secondary objectives

Collect data on the cost and resource use of health and social care services during the delivery of the interventionEvaluate the feasibility and acceptability aspects of the research design and procedures (e.g. screening, consent processes, recruitment and attrition rates and potential outcome measures) to help inform the planning and design of a future trial.

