### About the adapted nutritional intervention

The tailored nutrition intervention is based on the key principles of the person-centred nutritional care model (see Additional file 3: TOMATO logic model). The nutrition intervention targets home care professionals by delivering nutrition awareness training and providing them with adapted resources. These resources demonstrate various practical ways, including behavioural and environmental aspects, to take action and support people living with dementia at home with eating and drinking.

The intervention will be delivered by trained home care professionals in the homes of the participating dyads over a 4-month period.

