### Outcome measures and data collection

The primary outcome will be an assessment of study feasibility, including acceptability, recruitment and retention, protocol adherence and adaptations, compliance with study procedures including completion of questionnaires, percentage withdrawal, completion of outcomes and assessments, barriers and enablers to intervention delivery. We will relate the evaluation to focused components of feasibility studies [43]. This includes the assessment of acceptability, demand, implementation, practicality, adaptation, integration, and expansion. Secondary outcomes will be collected at baseline and 4-month after the first visit by the home care professional, unless recorded as routine data, at other time intervals. In such cases, all data recorded over the intervention period will be gathered. They will include nutritional status of the person with dementia (body weight, height to calculate Body Mass Index, BMI of < 20 kg/m^2^ as an indicator of undernutrition), quality of life using EQ-5D-5L/EQ-5D-5L-Proxy and DEMQoL/DEMQoL-Proxy [44–46] (as a robustness check and interview administered) and functional status (Deterioration in Daily Living Activities in Dementia) [47] and carer burden using Zarit Burden Interview [48]. Outcome measures were selected based on our logic model and informed by consultation with the PPI and Project Management Group. Table 4 outlines these assessments and strategies for measuring the outcomes of the TOMATO study.

**Table 4 Tab4:** TOMATO outcome measures

Feasibility parameter	How they will be assessed?		When the measures will be collected? [pre- only, post- only, pre and post intervention]
Recruitment rate	Percentage of participants recruited from participating home care provider		Pre and post
Attrition rate	Percentage of participants who drop out of the study before completion		Pre and post
Intervention Adherence	Percentage of staff who adhere to the intervention schedule (including the completion of the monthly action logs for 4 months)		Post-only
Components of focus			
Acceptability	Semi-structured interviews/focus group with participants		Post-only
Demand	Analysis of screening data Semi-structured interviews/focus group with participants		Post-only
Implementation	Documentary analysis Semi-structured interviews/focus group with participants		Post-only
Practicality	Semi-structured interviews/focus group with participants		Post-only

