### Nested process evaluation

As part of the study process evaluation, qualitative data will be generated from semi-structured interviews or focus groups conducted by the researcher at 4 months.

A sample of participants receiving home care and their carers (*n* = 12 dyads) will be invited to participate in semi-structured interviews. Family carers will be given the option to have a separate interview, and paid care for the person with dementia will be offered.

Home care professionals (*n* = 12), and home care managers (*n* = 4) will be invited to take part in an interview or a focus group (in pairs of 2–3 staff per provider organisation). We will adopt blended approaches, incorporating a combination of face-to-face interviews (using a Dictaphone) and online interviews/focus groups (via Zoom/Teams software), which will be video and/or audio-recorded and transcribed verbatim.

We will use a pre-designed topic guide, developed in conjunction with our PPI group consisting of key open-ended questions. Participants will be asked to feed back about various aspects of their experiences to inform a potential future trail including receiving or delivering the nutrition intervention, identifying priority areas, the delivery process, how the approach worked, the barriers, facilitators, and aspects that could be improved. For all participants, we will collect demographic data from home care records, including age range, gender, ethnicity, living arrangements, and dementia diagnosis.

Documentary analysis will be undertaken from a review of care plans of people with dementia (at baseline; during preceding 4-month period and at 4 months) using a checklist of key data, e.g. food and drink intake, weight recording, costs.

A bespoke document will be used to collect data on intervention fidelity and dose. This document will be completed by home care professionals, informal carers, or healthcare professionals, or via standardised recording in care plans. Implementation fidelity will be guided by a revised version of Carroll et al.’s conceptual framework [49].

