### Feasibility economic component

To estimate the associated costs, data will be collected on the use of health and social care services and support provided by family carers and friends, using a questionnaire adapted from and informed by existing tools such as the Resource Utilisation in Dementia-Lite Version (RUD-Lite) [50]. Data will be gathered from home care records, family carer dyads, and home care professionals.

Specifically, family carers will be asked about the number of hours they spend providing informal care. Data collected on resource use will relate to accessing healthcare, including hospital admissions, ambulance call-outs, length of hospital stay, personal social services, prescription data, and oral nutrition supplements.

This resource use will be costed as per conventional practice via the use of administrative data sets such as NHS Reference Costs, Personal Social Services Research Unit (PSSRU) Costs of Health and Social Care, and the NHSBSA Drug Tariff. Where relevant, missing cost and health-related quality of life data will be estimated using multiple imputation. Levels of missing data per cost category will also be reported.

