## Discussion

This study will determine the feasibility of our nutrition intervention to improve nutritional care for people with dementia receiving home care, which will inform the development and implementation of a future pilot RCT, should this be feasible. The feasibility study will measure resource use, identify key drivers of associated costs, and provide preliminary information for a future trial. This will be balanced against the costs of hospitalisation and the need for NHS resources associated with adverse events. Through the research, feasibility and acceptability data will be provided to understand the barriers and enablers for implementation. This knowledge will help guide implementation to facilitate greater uptake, adoption and spread into policy and practice in a future study.

Home care professionals are uniquely positioned to play a significant role in supporting people living with dementia. While previous RCTs [24, 25] have shown positive effects on quality of life and delayed nutritional decline through nurse- or multidisciplinary team-delivered nutrition interventions for older adults at home, evidence on interventions delivered specifically by home care professionals remains limited. The TOMATO study will address this gap and contribute valuable insights into the context-specific challenges faced by home care professionals in delivering nutritional care to people living with dementia who are in receipt of home care.

This study has potential far-reaching implications, as identifying nutrition-related health risks and intervening at an early stage for people with dementia living at home can help reduce deterioration in mental and physical health and wellbeing. As such this means there is increased potential for improved quality of life, maintenance of independence, reduced burden for family and home carers and increased likelihood of remaining at home for as long as possible. The study will produce new outputs, including new data, training and toolkit materials and as a feasibility study will be tested to improve the nutritional care of people with dementia living at home and receiving home care.

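### The resource-use analysis is limited to an undefined final month, although the secondary objective covers the whole 4-month delivery

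*Protocol article*

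**What the plan says.** The analysis rule is in the Protocol article, Data analysis, Quantitative: "We will analyse resource use data collected during the final 1-month follow-up period". The sentences after it deal with unit costs. They give no reason for the one-month window and no rule for scaling it up to the delivery period.

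Other sections describe a longer period:

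- **Secondary objectives:** "Collect data on the cost and resource use of health and social care services during the delivery of the" intervention.
- **About the adapted nutritional intervention:** "The intervention will be delivered by trained home care professionals in the homes of the participating dyads over a 4-month period".
- **Nested process evaluation:** care plans are reviewed at baseline, then "during preceding 4-month period and at 4 months) using a checklist of key data, e.g. food and drink intake, weight recording, costs".
- **Outcome measures and data collection:** where outcomes are recorded routinely, "all data recorded over the intervention period will be gathered".
- **Feasibility economic component:** the items to be costed concern access to healthcare, "including hospital admissions, ambulance call-outs, length of hospital stay, personal social services, prescription data, and oral nutrition supplements". The sources are home care records, family carer dyads and home care professionals. No recall period is stated.
- **Table 4:** the resource questionnaire is administered after the intervention only.
- **Discussion:** the study is to measure resource use and identify the main drivers of cost. It adds: "This will be balanced against the costs of hospitalisation" and the NHS resources linked to adverse events.

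**The concern.** The analysis section states a window that does not match the objective. This is a fixed rule in conflict with another part of the protocol, so it is not a detail that can be left to a later analysis plan. An analysis plan that followed the sentence would carry the mismatch forward.

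What is at stake is the usefulness of the cost data for planning a later trial. Admissions, ambulance call-outs and length of stay are episodic. They are likely to account for much of the cost and its variability, and a single month in about 25 dyads may show few of them or none. The window also sits at the end of follow-up, when the dyads still under observation are those who stayed. The Safety reporting section itself expects intercurrent illness to affect attrition and falls to lead to hospitalisation, so loss may be related to cost. Records from the earlier months of dyads who leave would be informative, and the stated rule leaves them out.

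**Working it through.** The plan gives no figure to reproduce here, so the check compares the analysis window with the period named in the objective.

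**Inputs from the protocol**

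- Delivery period: 4 months (About the adapted nutritional intervention).
- Analysis window: 1 month (Data analysis, Quantitative).
- Dyads: 32 enrolled, 25 expected at 4 months (Sample size).

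**Share of the objective's period left out**

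(4 − 1) / 4 = 0.75, so 75% of the delivery period lies outside the stated analysis.

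**Person-time = dyads × months**

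- Final month, 25 completing dyads: 25 × 1 = 25 person-months.
- Full delivery, 25 completing dyads: 25 × 4 = 100 person-months.
- Dyads expected to be lost: 32 − 25 = 7. Depending on when they leave, their observed time adds between 0 and 7 × 4 = 28 person-months. Full-period person-time is therefore between 100 and 128.

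**Illustration for an infrequent item**

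The documents give no admission rate. The rates below are assumptions, chosen only to show a range. With a Poisson count, expected admissions = rate × person-months, and the chance of none = exp(−expected).

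| Assumed admissions per person-month | Expected, 25 person-months | Chance of none | Expected, 100 person-months | Chance of none |
|---|---|---|---|---|
| 0.02 | 0.5 | 61% | 2 | 14% |
| 0.05 | 1.25 | 29% | 5 | 0.7% |
| 0.10 | 2.5 | 8% | 10 | under 0.01% |

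The percentages depend on the assumed rates. The direction does not: at any constant rate, the full period yields four times the expected events of the final month.

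**What the sources can supply**

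- The care-plan review and home care records are not tied to a single month, so for them the restriction leaves out information that the study plans to hold. The phrase about the preceding 4 months could be read as the time before baseline, but the review at 4 months still bears on the delivery period.
- Adverse events and serious adverse events are documented during the study (Safety reporting), so hospitalisations reported that way have no one-month limit either.
- For the post-intervention questionnaire, the period covered cannot be determined from the article.

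**The case against.** **The component is secondary and descriptive.** The objective is worded as collecting data, costs do not appear in Table 5, and the Discussion promises only preliminary information for a later trial. This stands, and it limits the severity. It does not remove the conflict, because the Discussion also promises to measure resource use and identify cost drivers.

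**The sentence may describe when data are collected, not the period they cover.** The wording allows this, and nothing in the article excludes it. Nothing supports it either, and on that reading the sentence would still need rewriting.

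**The statement on routine data is weak support.** The sentence "In such cases, all data recorded over the intervention period will be gathered" introduces a list of nutritional, quality-of-life, functional and carer-burden measures that does not include resource use. This is fair. The care-plan review, which names costs, is the stronger evidence.

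**Longer recall has its own cost.** This is true for items such as informal-care hours, and a one-month reference is reasonable there. It is not a reason to restrict records.

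A reader might also draw stronger conclusions that the documents do not support:

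- *That three months of all resource data are thrown away.* This holds only for record-based data. The questionnaire's reference period is not stated, so for it months 1 to 3 may never be collected.
- *That a dyad lost before month 4 contributes nothing.* The Feasibility economic component plans multiple imputation of missing costs where relevant and draws on home care records. Safety reporting says follow-up continues where possible. What stands is narrower: the stated window does not use the months actually observed in those dyads.
- *That admissions would go unseen.* Adverse-event reporting runs independently of the cost window. The probabilities above concern the cost analysis, not the whole study.
- *That the window causes the cost of staff training to be missed.* The objective concerns health and social care services. Training is a provider input that a wider window would not capture, so it is a separate matter.

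**Conclusion.** The point holds. The analysis section restricts resource use to a final month that is defined nowhere else, while the objective covers the 4-month delivery. Taken as a reference period, that leaves 75% of the objective's period out of the analysis and reduces 100 person-months to 25 for 25 completing dyads. The loss falls mainly on infrequent items, and record data from months 1 to 3 go unused.

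The conclusion rests on two assumptions: that the one-month phrase means the period covered, and that 25 dyads complete as planned. The admission rates only illustrate the effect and are not needed for the conclusion.

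Severity is should-fix. No progression criterion depends on costs, so the decision whether to proceed to a trial is not directly affected. The accuracy of the cost-driver findings is.

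**What to change.** Amend the resource-use sentence in Data analysis, Quantitative, so that it does the following:

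1. Analyse record-based resource use over the full 4 months, from home care records, the care-plan review and hospitalisations documented as adverse or serious adverse events.
2. Use observed time for dyads lost early, reporting events and costs per person-month alongside totals.
3. State the reference period of the post-intervention questionnaire. Keep one month for recall-sensitive items such as informal-care hours, and label those results as final-month estimates.
4. If only one month can be analysed for an item, narrow the secondary objective and the matching Discussion wording for that item.

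The cost is a few sentences of text and slightly more extraction and analysis work, with no extra participants. One limit remains: the Feasibility economic component names no hospital or general-practice records, so 4-month admission data would rest on home care records and adverse-event reports. Their completeness should be reported with the missing-data rates already planned for each cost category. The questionnaire's reference period should be settled before it is used, since months it does not ask about may not be recoverable later.

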#### Qualitative

Interview data will be transcribed verbatim, anonymised, and analysed using framework analysis (familiarisation, identifying a thematic framework, indexing charting, mapping and interpretation), including components of feasibility and NPT [39, 55]. Findings will be discussed with the PPI Group to guide interpretation. Researcher memos will be employed throughout the research, including interviews and focus groups, and these memos will be referenced during analysis.

NVivo Pro 20, a qualitative data analysis (QDA) computer software package will be used to facilitate the data analysis.

### Data management

Data will be managed using the Edge platform, the Local Portfolio Management System (LPMS), to capture TOMATO feasibility trial data and support the delivery and maintenance of the study, or an electronic database management system like REDCap, both of which comply with GCP requirements for data management.

All participants enrolled will be assigned unique participant identifiers. Data will be collected in paper or electronic format with various file formats including Microsoft Word, Portable Document Format (PDF), or Microsoft XLSX, based on preference. Electronic files will be transferred using a secure Bournemouth University (BU) file transfer system. All electronic files and the pseudonymisation details will be password-protected and stored on restricted-access folders on a BU secure server accessible only to authorised members of the study team.

All data collected on paper case report forms will be transferred securely using a Study Lockable Document Wallet or in a Travel Secure Rucksack with a lock (using a code or padlock). A delegated research team member will enter and upload participant anonymised data onto the local LPMS system, accessed only by authorised personnel. All paper copies will be stored in a secure BU site filing locker in a timely manner. All data will be archived in line with Bournemouth University’s information security policies and the archiving standard operating procedures.

As the study involves the collection and sharing of data from participating home care providers, risk management processes, including a Data Protection Impact Assessment (DPIA) and a Data Management Plan (DMP), will be in place to address and reduce any associated risks of the intervention and data security.

The TOMATO project team (Project Management Group), led by the chief investigator (JM), will hold monthly meetings to assess and monitor progress, review risks, and mitigate any problems arising. The TOMATO Project Steering Group (PSG) will provide independent oversight for the study.

All person identifiable data will be managed, stored and protected in accordance with the UK General Data Protection Regulation (UK GDPR) and the Data Protection Act 2018 (DPA 2018). Bournemouth University as the sponsor of the study will maintain an oversight of the study as per Good Clinical Practice (GCP) guidelines and the UK Policy Framework for Health and Social Care Research (2017). This includes monitoring of the study records to ensure adherence to GCP.

